### Interventions

#### Control Group

Participants in this group will continue with usual care. Usual care comprises medication, attendance at medical clinics, and review by PD nurses. Exercise therapy may be accessed but this is not routinely prescribed in the UK. As a way of encouraging adherence to follow-up at the end of the trial, participants in the control group will be offered vouchers to attend nontrial dance classes at the dance center.

#### Dance Group

In addition to usual care, participants will attend dance classes (with a healthy partner) at a local dance center, led by a professional dance teacher and supported by a second teacher and research fellow B (Figure 2). Classes will last 1 hour, twice a week for 10 weeks. The length and number of sessions was chosen following discussions with the dance teacher and based on results from published literature [6]. Care will be taken to ensure that the pace of teaching is appropriate and will reflect that recommended by Hackney and Earhart [6]. Class sizes will be small and supervision from both the dance teachers and research fellow B will minimize any risk of falling. Participants will learn 6 dances (3 ballroom and 3 Latin American dances). Each session will start with a warm-up, then new steps will be introduced and practiced, and a record of the session will be kept. Proposed dances included the social foxtrot, the waltz, the cha cha, ballroom tango, the rumba, and rock and roll. Emphasis will be placed on encouraging individuals to extend their postures, turn their heads and trunks, heel strikes, and toe push-offs because these movements are affected by PD and associated with changes in balance responses. The dance program will be tailored to individual capabilities in each class (the dance teachers will dance with couples who were struggling), and the research fellow will ensure the safety and well-being of participants and their partners. The research fellow will keep a record of each class, and some of the classes will be videotaped (with consent from participants).

**Figure 2 figure2:**
[figure not shown]
Participants enjoying a dance class.

### Assessments

Research fellow A will carry out baseline and follow-up assessments at 3 and 6 months and will be blinded to participant group allocation. Prior to each assessment, participants will be reminded not to reveal whether they have been dancing, and following each assessment the assessor will be asked to record awareness of group allocation. The assessments will be organized at similar times of the day, will last approximately 1 hour, and be completed in the person’s home approximately mid-point in the medication cycle.

Data collected for the anticipated primary outcome measures for the main trial will be the BBS [22], a categorical scale of balance activities (a high score is good with a maximum of 56), and spinal posture, which will be measured using the spinal mouse [25]. The spinal mouse is a handheld device that can measure the position and mobility of the pelvis, and lumbar and thoracic spine by recording the segmental angles as it is rolled over the spine. This device has been used with people with PD [26] and the data will describe angles of the participants’ spinal segments in the standing position and the overall degree of forward inclination in relation to upright. We used these tests in previous research studies [27].

At baseline, we will characterize our sample using the following measures: demographic data; measures of disease severity (Hoehn and Yahr Scale [19]; 1-5, high score is poor) and UPDRS motor section [23] (0-56, high score is poor); medication (using levodopa equivalent daily dose); freezing of gait questionnaire [20] (0-24, high score is poor); the Montreal cognitive assessment of cognitive function [21] (0-30, high score is good); and we will ask participants to retrospectively recall fall events during the previous 12 months using a standardized questionnaire [28].

Outcome measures will be recorded at baseline, and at 3 and 6 months and included the primary outcome measures, the Berg balance scale [22] and the spinal mouse [25]. The secondary outcomes include a measure of turning, the standing start 180° (SS180°) test in which the individual turns in both directions and the number of steps, time, and quality of turn are rated [29]; the timed up and go test, stand up from a chair and walk forward 3 meters and turn and return [30]; the PDQ39 (a self-completing questionnaire rating how hard it is to complete a range of everyday activities [31]; 0-100, low score indicates better health); the ABC, which is a questionnaire about balance confidence [32] (0-100, high score is good) ;the phone-FITT, a questionnaire delivered over the phone and designed to gather information about levels of the physical activity of older adults, such as how many times a week do you do housework activities such as tidying or dusting, walking, swimming [33], scoring is according to frequency of activities, duration, and intensity; and the Euroquol-5D, which is a simple quality-of-life measure [34] (1-5, high score is poor but a high visual analoge score is good).

At the final assessment, participants will be given a questionnaire about resource use that will be used in economic evaluation such as travel, refreshments, and buying shoes for the dance class and their views on the acceptability and benefits of the research project and to collate additional information needed for the economic evaluation. Participants will be asked to complete this questionnaire on their own time and to return it to the research team in the freepost envelope provided. We plan to ensure that the measurement battery is appropriate for use in a definitive multicenter phase III trial and not burdensome for the assessor or participants.

### Statistical Analysis

Feasibility issues will be addressed by examining numbers and percentages successfully recruited and completing various components of the trial protocol. The choice of outcomes for the main trial will be addressed by examining the completeness of data collection, relevance to issues raised as important by users, and comparison to related studies in the literature. The statistical analysis plan for the primary efficacy outcome in the main trial is currently envisaged to contrast the dancing and control groups (presented with 95% CI), after controlling for the primary outcome measured at baseline and center, either performed separately at 3, 6, and 12 months in analysis of covariance, or in a mixed model including both follow-up points. Depending on the primary outcome chosen, the corresponding modelling approach in logistic or Poisson models may be appropriate. Comparisons of outcome will be done on an intention-to-treat basis, with sensitivity analyses restricted to those completing the allocated interventions. The analysis of outcome data from the pilot randomized controlled trial, along with information from the literature, will inform the power calculation for the main trial. The current trial is not powered to demonstrate efficacy. We will examine the predictive power of baseline characteristics such as the Hoehn and Yahr severity, freezing of gait, and phone-FITT scores, to assess the benefit of additionally including them as stratifiers in the randomization of the main trial.

### Qualitative Substudy

#### Aim

The aim of the qualitative substudy will be to identify and explore the views of people with PD and their dance partners about the appropriateness and acceptability of the dance programs and the perceived impact on their mobility. Their views of the trial procedures will also be explored. An experienced qualitative researcher has been employed to complete this part of the study.

#### Methods

Fifteen of the 35 couples in the experimental group will be recruited to the qualitative study. Couples will be recruited with the aim of attaining maximum variation in the qualitative sample of the factors that may affect their experiences of the dance intervention, such as age, sex, and relationship with the dance partner.

#### Interviews

In-depth, semistructured, qualitative interviews will be conducted using an interview guide developed for the study. The interviews will be conducted in the home separately with the people with PD and their dance partners where possible (where couples are spouses this may not be possible) within 1 month of completing the dance program. With participants’ consent, the interviews will be audiorecorded and fully transcribed. For people with PD, the interviews will explore the following issues: their perceptions of the impact of PD on their day-to-day lives and their experience of physiotherapy or any other interventions since diagnosis that were designed to promote activity; and experiences with exercise activity (dance or other exercise activity) before their diagnosis of PD. The following issues will be explored with people with PD and their dance partners: their reasons for deciding to take part in the dance program and their perceptions and expectations of it, the number of sessions they attended and reasons for missing any sessions or dropping out, what it was like to take part, enjoyment of the activity, maintaining enthusiasm for the activity, the implications of working with a partner, perceptions of the impact of participating in the dance program, interest in continuing with dance classes or other activity, and their perceived impact on their mobility. Participants will also be asked about any personal costs they experienced while participating.

#### Analysis

Facilitated by QSR International’s NVivo 9.2 software, the data will be managed using Framework [35] and analyzed thematically to explore participants’ views about the acceptability and appropriateness of the dance program. Features of grounded theorizing and constant comparison will be used to identify and develop themes [36]. Data analysis will be undertaken by experienced social science qualitative researchers (JR and RW).

The framework is a staged approach that is well-suited to applied health research. In the first stage, the researchers will identify topics for an initial analytic framework based on prior understanding of the issues and concepts arising from close reading of the transcripts. In the second stage, participants’ accounts will be condensed on a case-by-case basis into charts according to the framework topics. The third stage will involve working through the data in detail to draw out themes or categories of experience that capture the full range of perspectives identifying commonalities and differences within and between participants.

The qualitative findings will be used to inform interpretation of the findings of the trial. Analysis of the qualitative data will take part in isolation from the trial researchers. Data from the qualitative study will be integrated at the end of the trial to avoid contamination.

Finally we will explore the views of those who choose not to take part in the study. Typically it is viewed as unethical or unnecessary to ask people to give reasons for declining to take part in research; however, in this study the information that is handed out as part of the recruitment process will give people the option to tell us if and why they find the dance intervention unattractive by completing an anonymous short questionnaire.

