Because this is a feasibility study, we will not be testing a hypothesis but will determine the methodological feasibility of evaluating the benefits of multiple dances taught through a dance center as a precursor to a definitive phase III trial. We need to understand how much dance people with PD and healthy partners will tolerate, which dances work best, how easy it is for dance teachers and dance centers to accommodate the needs of people with PD, and identify barriers and facilitators to participation in dance including the financial costs. We will build on the proof of principle studies [6-8] from the United States, address gaps in knowledge in planning a definitive trial of the impact of dance on balance and spinal posture, as well as turning, long-term follow up, economic evaluation, and user views. We will examine the appropriateness of primary and secondary outcomes currently envisaged for the future main trial and provide novel insight into user views on involvement in dance through a qualitative component, and develop procedures for economic evaluation for a future trial.

Specific questions of the feasibility study are:

1. What are the key routes to successful recruitment of healthy partners, people with PD, and dance centers to a randomized controlled trial of dance?

2. What are the most appropriate dances for people with PD?

3. How frequent, and how much dance is reasonable and likely to result in benefit for people with PD and healthy partners?

4. What specific adjustments do dance centers need to make regarding the delivery of dance to this group of people?

5. What level of dancing will be sustained to 3 and 6 months?

6. Will we obtain high quality data on spinal posture, balance, turning, and walking during home assessments?

7. Will we obtain high quality data on self-reported health status and balance confidence?

8. How appropriate and burdensome is the battery of assessments?

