### Participants With Parkinson Disease

Research fellow A will obtain informed consent and recruit 50 people with PD from outpatient services, local support groups (Parkinson’s UK), and the DeNDRoN (Dementia and Neurodegenerative Disease Research Network, a clinical research network for dementia and neurodegenerative conditions). Eligible people with PD will have a confirmed diagnosis of PD, Hoehn and Yahr [19] scale of 1-3 indicating mild-to-moderate mobility and stability; will be able to stand, turn, and walk safely and unsupported but may experience freezing of gait [20]; will live at home; understand and follow commands, through a screen for cognitive impairment [21]; and be able to tolerate the dance intervention. People with PD lacking sufficient stability to dance with another person in the clinical opinion of research fellow A (eg, in danger of losing balance control each time they turn around) will be excluded. The decision as to whether a potential participant with limited mobility can safely undertake the dance intervention will be based primarily on their performance on the Berg balance scale (BBS) [22] and the motor component of the unified Parkinson’s disease rating score (UPDRS) [23]. For example, someone scoring 0 on questions 7, 8, or 13 of the BBS, indicating inability to “stand unsupported with feet together,” inability “to attempt to reach forward” in standing without losing balance or inability “to stand unsupported with one foot in front of the other” will be considered ineligible. The UPDRS motor component gait questions 29 and 30 will also be used as indicators: a severe disturbance of gait that requires constant assistance or lack of postural stability to such an extent that balance is spontaneously lost in standing, will also discount potential participants.

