### Randomization

After the baseline assessment, eligible and consenting people with PD will be randomized to the dance or control group. Research fellow B obtained allocations by telephone from the trial medical statistician. Allocation will be randomized in 1 block of 11 participants (8 dance and 3 control), and 3 blocks of 13 (9 dance and 4 control), to yield participants entering each of 4 consecutive series of dance classes. The feasibility trial is too small to incorporate stratification. The dance-to-control ratio of 35:15 was chosen to maximize the number of people with PD experiencing the dance classes, while still including some control participants for feedback on the acceptability of randomization to control, retention, and fidelity in this group. The research fellow will contact participants to inform them of their allocation and of the times of their dance classes.

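### As described, the form for people who decline covers only the dance, so reasons for refusal that belong to the trial are not solicited from anyone who refused

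*Protocol article*

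**What the plan says.** The last paragraph of the Analysis part of the Qualitative Substudy states the aim: "Finally we will explore the views of those who choose not to take part in the study". It notes that asking decliners for reasons is usually seen as unethical or unneeded, and then gives the means. The recruitment literature is meant to "give people the option to tell us if and why they find the dance intervention unattractive by completing an anonymous short questionnaire".

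Three other places bear on the point:

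- The first feasibility question in the Introduction is "What are the key routes to successful recruitment of healthy partners, people with PD, and dance centers to a randomized controlled trial of dance".
- The Randomization section justifies including control participants partly by "feedback on the acceptability of randomization to control", sought within that group.
- The Statistical Analysis section says: "Feasibility issues will be addressed by examining numbers and percentages successfully recruited and completing various components of the trial protocol".

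No other section describes an instrument for people who decline.

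**The concern.** Declining a study and disliking its intervention are different things. The aim concerns the first, and the described form concerns the second. The purpose of this trial is to judge whether a definitive randomized trial can be run, so refusals caused by the trial's own features are among the most useful facts it could collect. Those features are chiefly the prospect of allocation to usual care and the assessments.

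If the only reasons gathered from decliners concern dance, the planners of the main trial could adjust the dance programme when the obstacle was the randomized design or the assessment load.

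**Working it through.** The plan states no figure for this point, so the check sets the sections side by side.

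**Step 1. Who is asked about what.**

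| Source in the protocol article | Who is asked | About what | Gives decliners' reasons? |
|---|---|---|---|
| Decliner form (Qualitative Substudy, Analysis) | People given the recruitment information | Whether and why the dance is unattractive | Yes, on dance |
| Control-arm feedback (Randomization) | Enrolled controls, 15 planned | Acceptability of allocation to control, retention, fidelity | No |
| Final questionnaire (Assessments) | Participants at the last assessment | Resource use; acceptability and benefits of the project | No |
| Interviews (Qualitative Substudy, Aim and Methods) | 15 of the 35 dance-arm couples | The dance programme and trial procedures | No |
| Recruitment and completion figures (Statistical Analysis) | Nobody is asked | How many, not why | No |

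Only the first row reaches people who refused, and its described content is the dance.

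**Step 2. Which reasons fall outside that content.**

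- *Dance itself*: covered.
- *No partner, travel, number of classes*: these are features of the intervention, which is partnered, held at a dance center, and runs twice a week for 10 weeks. A respondent can reasonably give them as what makes the dance unattractive, so they do not count as lost.
- *Chance of usual care*: belongs to the trial. The blocks give 3 + 3 × 4 = 15 control places out of 11 + 3 × 13 = 50, so 15/50 = 30%.
- *Assessments*: belong to the trial. Baseline, 3 months and 6 months at about 1 hour each make 3 × 1 = about 3 hours at home.

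The trial-only remainder is therefore mainly the last two.

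**Step 3. Whether another source fills the gap.** Enrolled controls and interviewed couples had all accepted randomization and assessment before they were asked. Their views describe people for whom these were not decisive obstacles. The counts show how many were lost and give no reasons.

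**Step 4. Timing.** Recruitment began in January 2013 and the last follow-up was expected in June 2014. With follow-up at 6 months after randomization, the last randomization would fall around December 2013. The article is dated July 2014. On those dates, forms from this trial may already have been returned.

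**The case against.** The strongest reply is that the form is not shown. One clause in a condensed article is being read as the full content of a questionnaire, which may have free text or further items. That stands as a limit on the wording: the most that can be said is that the form, as described, is confined to the dance. It does not remove the point, because the narrow content is stated, and it sits beside a broader aim in the same paragraph.

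A second reply is that asking whether dance is unattractive lets someone answer that it is not. That is fair, but such an answer shows that the reason lies elsewhere without saying what it is.

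A third reply is that the control-arm feedback was never assigned to the decliner form, and that none of the eight feasibility questions asks about refusal because of randomization. This is correct. The mismatch lies with the stated aim for decliners, not with a broken promise elsewhere.

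A reader might also infer that an anonymous form with no stated route marking leaves the first feasibility question unanswerable. The documents do not support that. The question asks which routes recruit successfully. Recruitment figures broken down by the sources named for people with PD ("from outpatient services, local support groups (Parkinson’s UK), and the DeNDRoN") can answer that part without linking any refusal to a route. Nor does anonymity prevent a route mark, since a code on each batch of forms identifies nobody. The article's silence on such coding is ordinary operational detail.

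**Conclusion.** The point holds as a mismatch between aim and described instrument. The plan, followed as written, does not solicit from decliners the reasons that belong to the trial rather than to the dance, and no other described source supplies them. The likely consequence is over-attribution of non-participation to the intervention.

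The size cannot be estimated. The article gives no number approached, number declining or number of forms expected, so the share of refusals made for trial-only reasons could be anything from negligible to substantial. Any percentage would be a bare assumption. Optional anonymous returns are also not a random sample of decliners, so a confidence interval around such a percentage would mislead.

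Two stronger statements should not be made. The first is that respondents are in fact led to blame dance, since nobody outside the trial has the form. The second is that partner, travel and class-frequency reasons are lost, since they can be given as features of the intervention. The conclusion assumes that the article's description reflects the form's content. It is worth acting on because the correction is cheap and serves the trial's main purpose.

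**What to change.** Keep the form short, optional and anonymous, and change its question to why the person decided not to take part in the study. Offer a tick-list that includes the dance itself, the chance of allocation to usual care, the assessments, travel, partner, health and other, with room for free text. Amend the sentence in the Analysis part of the Qualitative Substudy to match. The cost is a slightly longer form and a minor amendment.

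If forms have already been returned, rewording cannot recover the missing reasons. In that case, report the returns explicitly as views on the dance, do not present them as the reasons for non-participation, and use the wider question in the main trial. If the form in use already asks about trial-related reasons, correcting the description is enough.

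A non-identifying route code on each batch would allow reasons to be shown beside the recruitment figures by source. It is an optional extra that the first feasibility question does not require.
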